### Education tools for patients after FIT testing

#### Follow-up of negative screening tests

FIT kits are processed by the EFHC laboratory and results entered into their EHR. FIT results are sent to the CRC Screening Coordinator. If the FIT is negative, the Coordinator notifies the patient by mail; the letter (Additional file 1) includes a reminder that the test must be repeated in one year along with a reminder card. Our goal is to prime patients for the second round of reminders/mailings they will receive in one year and to encourage them to initiate contact on their own. This priming may be important because many patients may change phone numbers, addresses, or providers over the course of a year.

#### Follow-up of positive screening tests

Nationally, a high proportion of patients with a positive FOBT do not complete a diagnostic evaluation [24-32]. To address this, if the FIT is positive (i.e., blood detected), the CRC Screening Coordinator works with the patient’s physician to arrange follow-up colonoscopy. Patients are tracked and reminded until this is completed or until the patient refuses. The date of completed colonoscopy, findings, pathology results, and recommended date for repeat screening (if completely normal) or surveillance (if abnormal) are added to the patient’s problem list in the EHR.

During the first few months of the project, we learned that patients often struggled to understand the colonoscopy preparation instructions, which had high literacy and cognitive demands. This is consistent with previous research showing that colonoscopy preparation is suboptimal, which decreases the sensitivity of the test for finding polyps and may even require repeat colonoscopy [33,34]. Therefore, we applied the same methods described above for developing the FIT instructions to create simplified colonoscopy preparation instructions (see Additional file 1). We are also working to develop a video that explains to patients what a colonoscopy is and how it is performed to ease their concerns and maximize completion rates. Previous studies have reported that only 25-59% of patients with positive FOBTs undergo diagnostic colonoscopy [24,25,27-31,35-38]. Although our study was not designed to test whether the tools we developed will improve completion rates, we hope that this may be possible in future studies.

### Outcome assessment

The primary outcome for the study is completion of a FOBT within six months of the date when a patient first became due for repeat screening (i.e., one year after their qualifying FOBT). The outcome is assessed by querying the EHR for both intervention and usual care patients to determine if a FOBT screening test was completed. By relying only on the EHR for outcome assessment for both the intervention and usual care group, we hope to avoid any bias that might occur in the rates of detection of FOBT completion. Specifically, if the CRC Screening Coordinator was aware that a FIT was performed but the results were not documented in the EHR, the patient would still be classified as having not completed screening. Using only EHR data for outcome assessment is conceptually similar to blinded outcome assessment.

We have found that some patients randomized to the intervention have a repeat FOBT done at a clinical encounter shortly before the date that they are due for the intervention. The intervention is not conducted for these patients. Equal numbers of patients in the control group are expected to complete repeat testing prior to their due date, but we remain blinded to the outcomes in the control group. Because these patients were randomized prior to knowing their outcomes, we will include them in the main analyses.

### Power calculation

The repeat screening rate for patients at EFHC was not known at the time this study was designed because many eligible patients had only recently completed their first FOBT. We assumed that 35% of patients in the usual care group will achieve the primary outcome, similar to the rate in previously published studies. To detect a 10% difference (45% vs. 35%) with 80% power (2-tailed alpha = .05), we would need 752 patients (376 in each arm). This is less than the 800 patients that we estimated will be eligible for the study. We think intervention effects less than 10% are not important to detect because it would not be substantial enough to justify the efforts required to implement this type of an intervention in CHCs.

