#### Identification of eligible patients and randomization

We used structured query language (SQL) to analyze EFHC’s EHR data to identify eligible patients. The accuracy of the query was confirmed by reviewing 25 random patients identified as being eligible and overdue and 25 identified as not being overdue. The query was also used to obtain patients’ medical record numbers, demographics, preferred language, number of chronic medical conditions, number of visits to the clinic in the past 12 months, primary care provider, and contact information.

To prevent having patients in the same household being assigned to different groups, we first identified all eligible patients who had the same address (28 patients, 14 households). We then used a random number generator to assign households in the first half of the list to the intervention (N = 7) and the remainder to the usual care group (N = 7). This process was repeated for all remaining eligible patients (N = 422) with a unique address.

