Conversely, if the intervention is not effective or if rates are suboptimal despite the intervention, our findings will spur future research and policy analyses about alternative screening strategies to address disparities. Endoscopy is more sensitive than FOBT for CRC screening and needs to be conducted less often. However, the costs of endoscopy are higher and many CHCs have limited access to endoscopy. Although there are significant barriers to using endoscopy for CRC screening, previous studies have shown that nurses can be trained to do flexible sigmoidoscopy effectively and safely [40-43]. Endoscopy is an acceptable screening strategy among populations with CRC screening disparities [44-50]. A study of screening colonoscopy for patients in East Harlem (55% Hispanic, 33% African American) found that 66% of patients completed colonoscopy with the aid of a patient navigator [51]. In addition, other studies have found that many patients cared for in safety net settings would prefer endoscopy to FOBT [47,50,52]. Such screening alternatives may need increased scrutiny should our intervention fail to achieve high rates of annual screening.

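### The power paragraph relies on 752 to 800 patients, but the article's own count is 450, which gives about 58% power for the 10-point target instead of 80%

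*Protocol article*

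**What the plan says.** The Power calculation section sets the target: "To detect a 10% difference (45% vs. 35%) with 80% power", at a two-tailed alpha of .05. The usual-care rate is an assumption: "We assumed that 35% of patients in the usual care group will achieve the primary outcome". The section derives 752 patients (376 per arm) and then compares that need with the expected supply: "This is less than the 800 patients that we estimated will be eligible for the study". It also calls differences below 10 points too small to justify the effort of implementation, so 10 points is the smallest effect of interest.

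The section on identification of eligible patients and randomization reports what was found. For shared addresses: "we first identified all eligible patients who had the same address (28 patients, 14 households"). For everyone else: "This process was repeated for all remaining eligible patients (N = 422) with a unique address". Shared-address households were split seven and seven, and the rest were allocated by the same process.

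The Analytic plan includes all randomised patients in the primary comparison. The Discussion looks ahead to a disappointing result: "Conversely, if the intervention is not effective or if rates are suboptimal despite the intervention", in which case the findings are expected to prompt work on other screening strategies.

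**The concern.** The two sections give incompatible pictures of the trial's size. One presents a requirement of 752 as comfortably met by 800. The other accounts for every eligible patient and reaches 450. The randomisation section is in the past tense. The qualifying test must fall within one fixed year (March 2011 to March 2012), and the weekly mailing cohorts come from that same year, so no later source of patients is described.

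The error bears on the primary comparison. A reader of the power paragraph will take a non-significant result as fair evidence against a worthwhile effect, because the design is presented as having 80% power for the smallest effect that matters. If power is well below that, a non-significant result will often be compatible with both no benefit and a benefit the authors consider important. Turning from repeat stool testing to endoscopy on the strength of such a result would not be supported.

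**Working it through.** **Inputs**

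- From Power calculation: usual care p1 = 0.35; intervention p2 = 0.45; two-sided alpha 0.05 (z = 1.960); power 80% (z = 0.8416); stated need 376 per arm; expected supply 800.
- From the randomisation section: 28 patients in 14 shared-address households, plus 422 others. Since 28/14 = 2 and a shared address has at least two patients, each household has exactly two. Seven households per arm is 14 patients; 422/2 = 211. Total per arm: 14 + 211 = 225.
- From the Analytic plan: all randomised patients are analysed. No allowance for dropout is stated.

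**Step 1. Reproduce the plan's figure.** Pooled-variance formula for two proportions, with mean rate 0.40:

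n = [1.960 × √(2 × 0.40 × 0.60) + 0.8416 × √(0.35 × 0.65 + 0.45 × 0.55)]² / 0.10²

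= [1.960 × 0.6928 + 0.8416 × 0.6892]² / 0.01 = 375.6, so 376 per arm and 752 in total. This matches exactly. The expected 800 (400 per arm) would have given 82.4% power.

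**Step 2. Power at 225 per arm, same formula.**

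- SE under no difference: √(0.48/225) = 0.0462
- SE under the alternative: √(0.475/225) = 0.0459
- Power = Φ[(0.10 − 1.960 × 0.0462)/0.0459] = Φ(0.206) = 0.582

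The unpooled version gives 58.6% and the continuity-corrected version 54.4%.

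**Step 3. Difference detectable with 80% power at 225 per arm.** Solving the same equation from a 35% usual-care rate gives 0.1298, or about 48% against 35%.

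**Step 4. Precision at 45% against 35%.** The 95% half-width is 1.96 × √(0.475/n): 9.0 points at n = 225 and 7.0 points at n = 376. With a half-width near 9, any observed difference between roughly 1 and 9 points gives an interval containing both 0 and +10.

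**Step 5. Sensitivity.**

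| Variation | Power for 10 points |
|---|---|
| Usual care 20% | 69% |
| Usual care 25% | 64% |
| Usual care 30% | 60% |
| Usual care 35% (plan) | 58% |
| Usual care 40% | 57% |
| Usual care 45% | 56% |
| Household ICC = 0.5 (assumed), effective N 440.7, 35% usual care | 57.3% |
| Household ICC = 1 (assumed), effective N 436, 35% usual care | 56.8% |
| 422 read as the whole total (211 per arm), 35% usual care | 55.5% |

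The ICC rows use effective N = 422 + 28/(1 + ICC). Clustering is negligible because only 28 patients share an address.

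**Step 6. Size of the shortfall.** 450/752 = 60% of the stated need; 450/800 = 56% of the expected supply.

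**The case against.** The strongest reply is that the paragraph is a design-stage calculation. It says the local repeat rate was unknown, speaks of what would be needed, and calls 800 an estimate. It does not say that the randomised sample has 80% power, and its arithmetic is right. On this view the fault is a forecast that was not updated. That describes the cause fairly, but it does not remove the problem: the article already holds the actual count and still offers the estimate as assurance that the sample suffices. A separate analysis plan cannot explain this, because both figures are printed in the same document.

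Three narrower points have some force.

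- The Discussion sentence is a conditional about ineffectiveness or low absolute rates. It is not a rule that equates non-significance with no effect, so it shows only where a misreading could lead.
- The 58% depends on the assumed 35% usual-care rate and on a true effect of exactly 10 points. For 50% against 35%, 450 patients give about 90% power. Still, 10 points is the plan's own target, and power for it stays below 80% at every usual-care rate in the table.
- Removing the original calculation would hide why the trial was launched. It is better kept, labelled as the planning calculation.

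It is also true that allocation, outcome definition, the analysis set and type I error are unaffected.

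**Conclusion.** The concern holds. The article's 80% power for a 10-point difference requires 752 patients, and its own count of all eligible patients is 450. At that size, power is about 58% and the risk of missing a true 10-point effect is about 42%, roughly double the planned 20%. The difference detectable with 80% power is about 13 points, and the expected 95% interval is about ±9 points.

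These figures rest on the plan's 35% usual-care rate, two-sided 5% testing, equal arms of 225 and analysis of everyone randomised. The total of 450 is a sum of two printed numbers, but the wording of the two counts leaves no third group. Across usual-care rates of 25% to 50%, power for 10 points is 56% to 64%. Because this is the stated power of the primary comparison, it needs correcting.

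**What to change.** Revise the Power calculation section as follows.

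1. Keep the 752 as the planning calculation and label it so. Delete the sentence on 800 eligible patients, or mark it as an estimate that was not met.
2. Add that 450 patients were eligible and randomised (225 per arm). With a 35% usual-care rate this gives about 58% power for 45% against 35%, 80% power for about 48% against 35%, and an expected 95% confidence interval of about ±9 points.
3. State in advance that a non-significant result whose interval includes +10 points will be reported as inconclusive, and align the Discussion with that. The Outcome assessment section says the team has not seen usual-care outcomes, so this can still be set before results are known.

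The cost is wording only: no extra patients and no change to allocation, outcome or analysis. The stated power becomes less favourable.

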### Analytic plan

The rate of FOBT completion for the intervention and usual care groups will be analyzed with an intention to treat approach that includes all patients randomized; this will provide a true picture of the effectiveness of the intervention that will allow other health care providers (especially similar CHCs) to know the probable benefits of implementing this intervention across their health care center or system.

In addition, we will conduct a subgroup analysis stratified by the number of visits to the clinic during the follow up period to see if the intervention’s main benefit is to obtain CRC screening for patients with infrequent clinic visits. We will also examine the fidelity of the intervention, including the proportion of patients who did not receive the mailed FIT kit (i.e., returned to sender because of incorrect address), the proportion who had the text message completed, the proportion that had the automated call completed, and the proportion of automated calls answered a) in person or b) by an answering machine. We will conduct logistic regression to analyze the association between the components of the intervention that were received (both the number and type) and the likelihood of FIT completion. We will also assess the incremental value of the three-month outreach calls by the CRC Screening Coordinator.

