**Methods:**

In this RCT, patients who are due for repeat FOBT are identified in the electronic health record (EHR) and randomized to receive either usual care or a multifaceted intervention. The usual care group includes multiple point-of-care interventions (e.g., standing orders, EHR reminders), performance measurement, and financial incentives to improve CRC screening rates. The intervention augments usual care through mailed CRC screening test kits, low literacy patient education materials, automated phone and text message reminders, in-person follow up calls from a CRC Screening Coordinator, and communication of results to patients along with a reminder card highlighting when the patient is next due for screening. The primary outcome is completion of FOBT within 6 months of becoming due.

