#### Empowerment of medical assistants to offer CRC screening if overdue

EFHC also implemented a standing order that allowed MAs to recommend guaiac card FOBT screening during pre-appointment triage and vital signs measurement to patients who were age 50 or older and not up to date on CRC screening. If the patients agreed to take the FOBT cards home, the MA showed them how to use it and answered basic questions about the test. If patients had questions beyond the MA’s scope of practice, patients were told to discuss this during the provider visit. The provider also had a chance to reinforce the MA’s recommendation to perform the test or to attempt to change a patient’s decision if the patient did not agree to the screening when the MA offered the test.

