### Conceptual framework

Most quality of care problems are due to a combination of patient, provider, and system-level factors. Any one of these may be rate-limiting so that care remains suboptimal even if most other aspects of care are done well. For example, if the care team routinely recognizes when patients are due for CRC screening but the patient does not understand why s/he needs to be screened or the instructions are intimidating, the test may not be performed. For this study, we developed a conceptual framework of likely barriers to optimal care and then designed the multifaceted intervention to address each of these barriers (Table 2). We believe that the components of the intervention may each have small, incremental effects that are both additive and synergistic, although we will not be able to determine the incremental effects of all individual components (see analysis plan below).

**Table 2 T2:** Conceptual framework for the intervention components

**Barrier**	**Intervention component(s) to address barrier**
No clinical systems in place to identify patients who need repeat screening, unless they present for care	EHR query to identify patients due for repeat screening; outreach to patients (half randomized to intervention)
No personal systems in place for patients to track when preventive services are due	Automatic phone/text reminders to remind patients they are due for screening
Low adherence to repeat screening because of financial and/or logistical barriers	Mail FOBT kits to patients
Patients forget to return FOBT	Automatic phone/text reminders to patients who do not return FOBT within 2 weeks
Low priority and/or risk perception for CRC	Call from CRC Screening Coordinator at 3 months to patients who do not complete FOBT to explain need for screening
Change of phone number and/or address makes initial reminders unsuccessful	When CRC Screening Coordinator calls at 3 months, he can use updated information (i.e., from a recent visit)
Patients do not understand instructions	Mailed FOBT kits include plain language information, instructions, and direct phone number for CRC Screening Coordinator

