### Two-phase intervention

#### Initial intervention

We group patients into weekly cohorts based on the date of their eligible FOBT between March 2011 and March 2012. Every Monday, all patients due for repeat FOBT screening in the coming week have a FIT kit mailed to their home, along with a letter from their primary care provider and the FIT instructions. We then send the automated phone call and two days later a text message via the commercial system (CallPointe; Tuscon, AZ) that EFHC uses routinely for patient reminders and health promotion messages. The system software allows us to track the number of completed phone and text messages, and whether the phone message is answered by a person or a machine.

Two weeks after the initial reminders and FIT kit mailing, we query the EHR to identify patients who did not return the mailed kit. Those who do not return the kit receive another automated phone call and text message.

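### The planned subgroup analysis stratifies on clinic visits during follow-up, which assignment may change; visits before randomisation are already extracted and should define the strata

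*Protocol article*

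**What the plan says.** The Analytic plan first sets out an intention-to-treat comparison of all randomised patients and then adds that "we will conduct a subgroup analysis stratified by the number of visits to the clinic during the follow up period". The stated purpose is to see whether the intervention's "main benefit is to obtain CRC screening for patients with infrequent clinic visits". This is the only subgroup analysis that the article names. The article gives no reason for counting visits during follow-up and makes no provision for assignment affecting them.

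Four other places bear on the choice:
- Identification of eligible patients and randomization: the query that found eligible patients also returned the "number of visits to the clinic in the past 12 months".
- Empowerment of medical assistants: a standing order "allowed MAs to recommend guaiac card FOBT screening during pre-appointment triage and vital signs measurement", so usual care offers the test at a visit. Table 2 (Conceptual framework) describes the barrier without outreach as "No clinical systems in place to identify patients who need repeat screening, unless they present for care".
- Initial intervention: "all patients due for repeat FOBT screening in the coming week have a FIT kit mailed to their home", followed by automated calls and texts, and by coordinator calls at three months for those not yet screened.
- Follow-up of positive screening tests: "the CRC Screening Coordinator works with the patient’s physician to arrange follow-up colonoscopy".

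**The concern.** Randomisation makes the arms comparable on anything fixed beforehand. It gives no such protection within groups formed by something that happens afterwards and that assignment can influence. Follow-up visits are of that kind, and the article describes routes in both directions. Reminders, coordinator calls and work-up of a positive result could add visits. A kit that arrives by post could remove a reason to come in.

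If either happens, a given visit stratum holds a different mix of patients in each arm, and the difference within it combines the treatment effect with the change in mix. The question asked is whether the benefit is concentrated in infrequent attenders. A shift in visits can produce that pattern where none exists, or mask it where it does. The result alone would not show which had happened.

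**Working it through.** **The plan's own figure.** For 45% vs 35% with two-sided alpha 0.05 and 80% power, the pooled-variance formula without continuity correction gives 376 per arm, 752 in total, as the article states. The present point does not change that figure.

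**Illustration 1: outreach adds visits.** From the article: 35% completion in usual care and a 10-point benefit. Assumed: two equal halves of patients, with Poisson mean visits in follow-up of 0.5 and 2 and usual-care completion of 25% and 45% (average 35%); a true benefit of exactly 10 points in both halves; and a share g of intervention completers who gain one visit.

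- Share with no visit before any shift: 0.5·e^(−0.5) + 0.5·e^(−2) = 0.3709. Share with one or more: 0.6291.
- Usual-care completion: 0.1063/0.3709 = 28.6% with no visit; 0.2437/0.6291 = 38.7% with one or more.
- Intervention completers before any shift, as a share of the arm: 0.1434 with no visit and 0.3066 with one or more.
- Intervention rate with no visit: 0.1434(1 − g)/(0.3709 − 0.1434g).
- Intervention rate with one or more visits: (0.3066 + 0.1434g)/(0.6291 + 0.1434g).

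| g | Difference, no visit | Difference, 1 or more visits |
|---|---|---|
| 0% | 10.0 | 10.0 |
| 3% | 9.3 | 10.3 |
| 10% | 7.5 | 11.1 |
| 20% | 4.9 | 12.2 |

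The true effect is 10 points in every row. The spread arises only because completers leave the no-visit stratum in one arm.

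**Illustration 2: outreach removes visits.** Assumed: 5% of patients, with 70% usual-care completion, attend only if assigned to usual care. A further 57.5% attend in either arm (40% completion in usual care). The remaining 37.5% attend in neither; an overall rate of 35% fixes their completion at (0.35 − 0.575·0.40 − 0.05·0.70)/0.375 = 22.7%. The true benefit is again 10 points throughout.

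- Attenders: 50.0% − (0.575·40% + 0.05·70%)/0.625 = 50.0% − 42.4% = 7.6 points.
- Non-attenders: (0.375·32.7% + 0.05·80%)/0.425 − 22.7% = 38.2% − 22.7% ≈ 15.6 points.

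The apparent gradient now runs the other way, towards the pattern the analysis is looking for. The 5% and 70% are assumptions, and the 70% is chosen to make the mechanism visible.

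**Baseline strata.** Visits counted before randomisation cannot be moved by assignment, so a uniform 10-point effect is 10 points in expectation in every baseline stratum under either illustration.

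**The case against.** A reader might go further and infer that, because usual care offers the test at visits, a usual-care patient with no visit cannot complete one, so that a large benefit in that stratum is guaranteed and therefore artefactual. The documents do not support this. Cards are taken home, and the Outcome assessment section says that some patients repeat the test at an encounter shortly before their due date and stay in the main analyses. Zero completion is therefore not built in. More importantly, if assignment does not change visits, follow-up strata are comparable between arms, and a larger difference among non-attenders is a true effect. Usual care that reaches mainly attenders is a mechanism, not a bias.

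Large shifts are also hard to defend from the text. Kits and negative results go by post. The positive-test section describes colonoscopy arranged with the physician and does not state an extra clinic visit. The low rows of the first table may be the more realistic ones, and there the distortion is about one point.

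Finally, the baseline variable is not perfect. Table 1 requires a screening code recorded as an encounter diagnosis in the year before the study, so nearly every patient has at least one baseline encounter. Patients whose due date falls late may also have a baseline count that is several months old when their follow-up begins.

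All of this stands, and it limits the size of the point. It does not supply a reason for preferring a variable exposed to assignment when one that is not is already in hand.

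**Conclusion.** The choice of subgroup variable should be changed. The article fixes it explicitly, so this is not a detail left to an analysis plan. The distortion depends on how far assignment moves visits, for which the documents give neither size nor direction. Under the first set of assumptions it runs from about 1 point between strata (9.3 vs 10.3) to about 7 (4.9 vs 12.2), and under the second it reverses. These figures show what is possible; they do not estimate the bias in this trial.

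The consequence is confined to the conclusion about infrequent attenders. The intention-to-treat comparison, the sample size and the primary outcome are untouched. If infrequent attenders do show a larger benefit, it may be genuine. The difficulty is that the planned strata cannot separate a genuine gradient from one caused by a shift in visits.

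**What to change.** In the Analytic plan, define the main subgroup strata by the number of clinic visits in the 12 months before randomisation. Choose cut-points for a population in which nearly everyone had at least one encounter in that year, for example 1 vs 2 or more, or tertiles, and not a zero-visit stratum. Report the risk difference with its confidence interval in each stratum, and an arm-by-visits interaction test. Tabulate follow-up visits by arm, which would show whether assignment moved them on average, and label any analysis stratified on them exploratory.

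The cost is a few lines of text, because the eligibility query already returns the variable. There are two limits. Baseline visits predict attendance in follow-up imperfectly, so a true gradient will look somewhat diluted. Precision is also modest whichever variable is used. The article reports 28 + 422 = 450 eligible patients; with two equal strata, about 112.5 per arm in each, the standard error of the difference between two risk differences is √[2(0.35·0.65 + 0.45·0.55)/112.5] ≈ 9.2 points. The interval should therefore carry the interpretation, and a non-significant interaction should not be read as no difference.
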